### Pharmacogenomics

There is considerable inter-individual variability in the disposition of drugs, and at least some is caused by polymorphisms in genes coding for drug-metabolizing enzyme and transporters. Some recent reports confirmed the need of pharmacogenetic studies to elucidate the ethnic or racial differences in drug disposition (pharmacokinetics - PK) which can occur at any step of drug disposition, absorption, distribution, transport, metabolism or excretion, drug-drug interactions and drug effect or tolerance, and pharmacodynamics (Haas, 2005, Telenti and Zanger, 2008). Any increase or decrease in drug concentrations and exposure will impact on efficacy and tolerance. The present pharmacogenetic sub-study could be helpful for a better understanding of variability in rifabutin or antiretroviral PK and of occurrence of adverse events in co infected tuberculosis and HIV Vietnamese patients included in the ANRS12150b study who accept to participate in this sub-study.

The objective of the present study is to identify in the included population single base mutations (Single Nucleotide Polymorphism SNPs) within genes involved in drug metabolism and transport. This will allow identification of patients carrying allelic variants encoding for loss of function enzymes or transporters. The SNPs will be selected according to the literature and the SNP database. The frequency of SNPs varies between populations.

The current study aim is to evaluate the best rifabutin dosing regimen when coadministered with lopinavir/ritonavir in HIV-infected patients. Lopinavir and ritonavir are CYP3A4 substrates and ritonavir is a potent CYP3A inhibitor which increases the concentrations of lopinavir. Pharmacogenetics of antiretroviral drugs has been recently reviewed by Telenti and Zanger (2008). Unlike rifampin, some rifabutin and most of its partially active 25-desacetyl-rifabutin metabolite (hereafter, *desacetyl-rifabutin*) are cleared by CYP3A4 (Iatsimirskaia et al. 1997). Although CYP3A4 is the major form in adult liver, in some populations CYP3A5 can make a significant contribution in subjects with low CYP3A4 activity. Although polymorphism in CYP3A4 have controversial effects on expression, CYP3A5 is highly polymorphic. The *CYP3A5\*3* allele (G at position 6986) creates a cryptic splice site creating aberrant mRNA, with a premature stop codon. Individuals with at least one A allele (*CYP3A5\*1*) produce high levels of full-length CYP3A5 mRNA and express an active CYP3A5 enzyme, while those carrying the *CYP3A5 6986 GG (CYP3A\*3)* genotype have very low or even undetectable hepatic CYP3A5 protein content. Most Caucasian expressed the loss of function *CYP3A5 6986GG* genotype associated with a small amount of translated CYP3A5 protein with a G

allele frequency ranging from 0.87 to 0.94 in various Caucasian populations. In contrast, in various Asian populations G allele frequencies were lower ranging from 0.59 in Indians to 0.67 in Vietnamese and 0.74-0.78 in Japanese, Chinese and Koreans (Veiga et al., 2009, Hiratsuka et al. 2002). The frequency is even lower in patients of African descent (0.36) (Haas et al., 2004). Higher expression of CYP3A5 protein will lead to an increase in clearance of CYP3A substrate drugs such as HIV-1 protease inhibitors. Lower saquinavir, atazanavir or indinavir concentrations were demonstrated in patients who express CYP3A5, although disposition of lopinavir combined with ritonavir, which inhibits both CYP3A4 and CYP3A5, remains unaffected (Estrela et al., 2009). Effect of CYP3A5 genetic polymorphism on rifabutin and its metabolite disposition is currently unknown.

More recently, the effect of uptake and efflux transporters on drug disposition was recognized. P-glycoprotein (ABCB1) transporter, which is encoded by the ABCB1 (MDR 1) gene, has a broad substrate specificity and plays an important role in reducing drug bioavailability and intracellular drug concentration. A number of studies have investigated the functional consequences of variation in this gene particularly the ABCB1-3435C>T polymorphism. This variant has been associated with mRNA, protein and serum levels, and with responses to a number of drugs (Loeuillet et al., 2007). Plasma concentrations of the protease inhibitors and CD4 cell count response have been associated with the T allele at the MDR1 C3435T locus (Saitoh et al., 2005). However, other studies (Ma et al., 2007, Estrela et al., 2009) did not confirm a correlation between trough plasma concentrations of atazanavir or lopinavir and the variant T allele. More recently, SLCO1B1 (OATP, organic anion transporting polypeptide) polymorphism was found to affect lopinavir pharmacokinetics (Lubomirov et al., 2010).

Two major families of hepatic enzymes are involved in the hepatic elimination of isoniazid (N-acetyltransferase 2 (NAT-2) and Glutathion-S-Transferases (Mu, theta et pi: GSTM1, GSTT1 et GSTP1). These are subject to marked pharmacogenetic variation, and different combinations of SNPs in the NAT and GST genes lead to different phenotypes (NAT2: low or fast acetylator). Genetic polymorphism could confer changes in liver susceptibility to those treatment combinations.

Rifamycins (rifampicin and rifabutin), are well known for their ability to induce drug-metabolizing enzymes and transporters, although rifabutin to a lesser extent, through activation of a nuclear receptor: the Pregnane X Receptor (PXR). It is now accepted that drug-dependent induction of genes important for drug disposition is mediated by nuclear receptors pregnane X receptor (PXR) (Tirona et al. 2005, which function as key ligand-activated transcription factors that control the expression of drug metabolizing enzymes and transporters. In comparison with other genes, relatively few single nucleotide polymorphisms (SNPs) are observed in hPXR. The single amino acid variants identified in subjects of Caucasian and African origin include amino acid changes in or close to the Ligand Binding Domain (R122Q (PXR\*4), V140M, D163G, and A370T) and others in the N-terminal region (E18K, P27S (PXR\*2), and G36R (PXR\*3). The most frequent of these,

P27S, was identified in 14.9% of chromosomes from subjects of African origin, whereas the others had allele frequencies below 3%.

Our main goal is to select some “target” functional SNPs and genotype our population to identify the impact of those different genes on PK and PD variabilities. We will focus on the association between rifabutin-lopinavir/ritonavir pharmacokinetics and genetic polymorphism of CYP3A5, ABCB1, OATP1B1 and PXR genetic polymorphisms. NAT2 and GST polymorphism will be related to liver toxicity if any. Any new data on these drug pharmacogenetics or unexpected results of the pharmacokinetic/pharmacodynamic study or tolerance could lead to study other allelic variant of drug metabolizing enzymes or transporters.

## **II. Project Objectives:**

### **2.1 Primary objective:**

To determine the pharmacokinetics of RBT in combination with ARVs in immuno-compromised patients with tuberculosis in Vietnam.

### **2.2 Secondary objectives:**

1. To compare the bioavailability of two different doses of RBT in combination with LPV/r, with the bioavailability of RBT taken without ART in Vietnamese HIV infected patients with pulmonary tuberculosis and advanced immunodeficiency.
2. To determine the bioavailability of LPV/r in combination with RBT in Vietnamese TB patients with advanced immunodeficiency.
3. To determine the outcomes of tuberculosis treatment with rifabutin 150 mg once per day or thrice per week in combination with LPV/r during the initial phase of tuberculosis treatment.
4. To determine the safety and toxicity of RBT in combination with ART during the initial phase of tuberculosis therapy in Vietnamese patients.
5. To assess the genetic differences that may affect the response to antiretroviral and tuberculosis treatments.

## **III. Study Design**

This is a randomized, open-label, multi-dose, 2-arm, cross-over, clinical trial, investigating the bioavailability of RBT in combination with LPV/r.

## 1. Selection of patients:

### 1.1 Pre-screening

The recommended standard of care at Pham Ngoc Thach Hospital is for all newly diagnosed TB patients to be offered an HIV test, and CD4 lymphocyte count analysis if found to be HIV. Therefore, male or female individuals, aged 18 to 65 years (inclusive), with newly diagnosed pulmonary tuberculosis, who are HIV positive and have a CD4 less than or equal to  $250/\text{mm}^3$  identified in Pham Ngoc Thach Hospital, will be eligible for the study.

### 1.2 Screening

Subjects attending the screening appointment who have volunteered to participate in the study will be requested to sign an informed consent form in accordance with international GCP standards. They will then undergo a full clinical evaluation and the following screening tests to determine eligibility for enrolment (blood samples taken will be approximately 25 ml):

- Full clinical examination, including ophthalmologic examination
- Full Blood Count (FBC) - Haemoglobin, platelet and differential white cell counts.
- Urea and electrolytes (U&E) - Sodium, potassium, urea, creatinine, bicarbonate
- Liver Function Tests (LFT) - Total bilirubin, aspartate and alanine aminotransferase, albumin, alkaline phosphatase
- Amylase
- HIV test
- CD4 count
- Urinary pregnancy test
- Urinalysis
- Chest X-ray (CXR)

### 1.3 Inclusion:

#### 1.3.1. Inclusion Criteria:

Patients will be eligible for inclusion in the trial if they fulfil the following criteria:

- i. Having a diagnosis of pulmonary tuberculosis defined as:
  - a) at least 2 sputum smears positive (equal to or exceeding grade 1) for AFB; or
  - b) 1 sputum smear positive for AFB and a chest radiograph (CXR) compatible with active tuberculosis; or
  - c) 1 sputum culture positive for *M. tuberculosis* and a CXR compatible with active tuberculosis

- d) A CXR compatible with active tuberculosis and a clinical history suggestive of tuberculosis and 2 sputums smear negative for AFB
- ii. Positive HIV antibody test and a CD4 lymphocyte count less than or equal to 250/mm^3. Weight >40 Kg.
- iii. Having received no ART at all
- iv. Having no grade 3 or 4 clinical or laboratory findings according to DMID tables.
- v. If a female of childbearing age, having a negative pregnancy test on day of enrolment and willing to take appropriate contraceptive measures during the duration of the trial.
- vi. Having a firm home address that is readily accessible
- vii. Have a Karnofsky score  $Q \geq 80\%$

### 1.3.2. Non inclusion Criteria:

Patients who meet any of the following criteria will not be eligible for the study:

- i. History of TB (within last 12 months) or MDR TB treatment (at anytime)
- ii. Concomitant opportunistic infection (OI) requiring additional anti-infectious treatment
- iii. A formal contraindication to any drug used in the trial
- iv. Diabetes mellitus requiring drug treatment
- v. Recreational drug or alcohol abuse
- vi. History of drug hypersensitivity to TB or related medications
- vii. Mental illness that could impair ability to give informed consent or result in poor adherence to trial protocol and therapy.
- viii. Neutropenia (total neutrophil count < 1200 cells/L)
- ix. Anaemia (haemoglobin <6.8 g/dL)
- x. Requiring concomitant medications that may potentially interact with study drugs
- xi. Liver Function Test > grade 2
- xii. Pregnant or lactating women
- xiii. Karnofsky score  $Q < 80\%$
- xiv. Any condition rendering the patient unable to understand the nature, scope, and possible consequences of this study and to provide consent.

Grading for the purposes of evaluating inclusion criteria will be according to the Division of Aids table for grading the severity of adult and paediatric adverse events (published December, 2004).

## 1.4 Randomisation

Participants will be randomized to receive one of the individual treatment arms on day of enrolment..

Randomization lists will be produced prior to the start of the trial, indicating a randomization number and

which treatment arm to assign to a participant. The code for each individual will be provided in a separate sealed envelope and assigned to the individuals in the order in which they are enrolled in the study.

[figure not shown]

Figure 1: Diagram showing the timing of the trial procedures relative to trial visits and treatments (Rmp= rifampin, Inh= isoniazid, PzA= pyrazinamide, Emb=ethambutol).

## 2.2. ARV selection:

LPV/r will be at a dose of 400 mg/100mg twice daily (film coated tablets). The NRTI backbone will be lamivudine (3TC) 150mg twice daily in combination with stavudine (d4T) 30mg twice daily. LPV/r has been selected as the protease inhibitor drug for evaluation in this project because it is the most widely available second-line drug, and has an excellent long-term efficacy and safety profile. The availability of the new film-coated tablets that do not require refrigeration is particularly attractive for eventual use in warm climate countries. Participants intolerant to d4T, and requiring a change of therapy, will be allowed to switch to zidovudine 300mg BD without withdrawal from the trial. If AZT or Tenofovir becomes the standard of care for first line treatment of HIV in Vietnam either of these drugs can be substituted for d4T. Intolerance to any of the other antiretroviral drugs necessitating their substitution will require that the participant is withdrawn from the trial.

## 2.3 RBT Dosing

The international guidelines for use of RBT in combination with ARVs is 150mg TPW or on alternate days with LPV/r (17, 18). These guidelines are based on limited existing data, and there is still uncertainty if these doses are optimal. Co-administration of LPV/r with RBT is reported to result in large increases in RBT AUC0-24(22) which supports a dose reduction of RBT to 150mg TPW. However these results are from a limited number of healthy volunteers, and rifamycins concentrations may be lower in immunocompromised HIV positive individuals (16). Furthermore there are some recent anecdotal reports suggesting the 150mg intermittent dose of RBT is inadequate (23, 24). Therefore 150mg RBT daily will also be evaluated in this proposal.

The development of acquired rifamycin resistance (ARR) in HIV positive tuberculosis patients treated with intermittent chemotherapy regimens has been reported with rifabutin-based regimens (25), and was associated with low CD4 lymphocyte counts (<100) and highly intermittent regimens (once or twice weekly). It is unknown if thrice weekly dosing with these agents would also favour the emergence of resistance. A recent retrospective study from USA found that ARR was also associated with intermittent rifampin regimens, suggesting that the emergence of resistance is a rifamycin class effect, rather than one restricted to the longer

acting agents rifabutin and rifapentine (26). Given these uncertainties this protocol has adopted daily rifabutin dosing (except for the low dose rifabutin in combination with LPV/r which will be thrice weekly) which is compatible with the Vietnamese TB control programme schedule of daily dosing.

### **3. Outcome measures:**

#### **3.1 Primary outcomes:**

The primary study objective is to compare the pharmacokinetics of two different doses of RBT in combination with LPV/r, with the pharmacokinetics of RBT taken without ART in HIV infected patients with pulmonary TB and advanced immunodeficiency. The pharmacokinetics of RBT without ARV will be measured by the area under the curve ( $AUC_{0-24}$ ), and compared to the  $AUC_{0-24}$  for each of the RBT doses in combination with the ARV (and  $AUC_{0-48}$  in case of the three times weekly LPV/r arm).

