**ANRS 12150**
**Detailed Summary**
Objectives:

- Primary: to determine the pharmacokinetics of RBT in combination with ARVs in Vietnamese HIV infected patients with pulmonary TB.
- Secondary:
1. to compare the bioavailability of two different doses of RBT in combination with LPV/r, with the bioavailability of RBT taken without ARVs;
  2. to determine the bioavailability of LPV/r in combination with RBT;
  3. to determine the outcomes of tuberculosis treatment
  4. to determine the safety and toxicity of RBT in combination with ARV during the initial phase of tuberculosis treatment.
  5. to assess the genetic differences that may affect the response to antiretroviral and tuberculosis treatments.

Methodology:

Randomized, open-label, multi-dose, 2-arm, cross-over clinical trial

Inclusion criteria: newly-diagnosed TB patients with HIV infection

Patients will be eligible for inclusion in the trial if they fulfil the following criteria:

- i. Having a diagnosis of pulmonary tuberculosis defined as: a) At least 2 sputum smears positive (equal to or exceeding grade 1) for AFB; or b) 1 sputum smear positive for AFB and a chest radiograph (CXR) compatible with active tuberculosis; or c) 1 sputum culture positive for *M. tuberculosis* and a CXR compatible with active tuberculosis; or d) a CXR compatible with active tuberculosis and a clinical history compatible with tuberculosis and 2 sputums smear negative for AFB.
- ii. Positive HIV antibody test and a CD4 lymphocyte count less than or equal to  $250/\text{mm}^3$  at the pre-screening visit.
- iii. Weight > 40 Kg.
- iv. Having had no ART at all
- v. Having no grade 3 or 4 clinical or laboratory findings according to DMID tables.
- vi. If a female of childbearing age, having a negative pregnancy test on day of enrolment and willing to take appropriate contraceptive measures during the duration of the trial.
- vii. Having a firm home address that is readily accessible
- viii. Have a Karnofsky score  $Q \geq 80\%$

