#### 5.9 Pharmacokinetic analysis:

On each series of drug plasma concentrations, the following pharmacokinetic parameters will be determined, using the software package WinNonLin (Pharsight Corporation, California).

- Area under the curve for plasma concentration vs. time, until the last sampling time after dosing (AUCt)

- Peak plasma concentration ( $C_{\max}$ )
- The trough plasma concentration at the last time of sampling, immediately before the next dose.
- Time to peak plasma concentration ( $T_{\max}$ ).
- Half-life ( $T_{1/2}$ ).

The PK measures will be summarized using parametric or nonparametric methods (as appropriate). For RBT, the results from PK1 will be compared to PK2 and PK3, respectively. PK2 and 3 will be compared for all the drugs. The significance of differences between the pharmacokinetic measures will be determined using the Student t-test (parametric data) and the Wilcoxon signed rank test (nonparametric data). Bioequivalence analysis will be conducted using ANOVA for the AUC and  $C_{\max}$  values. The geometric mean ratios and their 90% confidence intervals will be reported. In addition the inter-individual and intra-individual variability will be evaluated for the PK measures. No interim PK analyses are planned. In addition, potential polymorphisms in specific enzymes involved in drug metabolism will be investigated.

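### Section 3.1 calls primary the comparison that section 2.2 and both summaries list as secondary objective 1, and section 5.9 defines the rifabutin contrasts by visit although each visit mixes both doses.

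*Protocol*

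**What the plan says.** **Ranking of objectives.** Section 2.1 gives the primary objective as "To determine the pharmacokinetics of RBT in combination with ARVs in immuno-compromised patients with tuberculosis in Vietnam". Section 2.2 lists as secondary objective 1 "To compare the bioavailability of two different doses of RBT in combination with LPV/r, with the bioavailability of RBT taken without ART". The English summary ranks its objectives the same way, with "to compare the bioavailability of two different doses of RBT in combination with LPV/r, with the bioavailability of RBT taken without ARVs" as secondary objective 1, and so does the French summary.

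**Outcomes.** Section 3.1 says "The primary study objective is to compare the pharmacokinetics of two different doses of RBT in combination with LPV/r", the comparator being RBT without antiretrovirals. The measure is AUC0-24, with RBT alone compared with the value "for each of the RBT doses in combination with the ARV"; AUC0-48 is added for the thrice-weekly dose. Section 3.2 places lopinavir AUC0-12, tuberculosis cure and adverse events among the secondary outcomes.

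**Sample size.** Section 4 rests on 12 participants giving 80% power for a 20% difference in mean AUC0-24 between RBT alone and RBT with antiretrovirals. It aims for 24 evaluable patients and allows up to 32.

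**Analysis.** Section 5.9 says "For RBT, the results from PK1 will be compared to PK2 and PK3, respectively" and "PK2 and 3 will be compared for all the drugs". It plans t or Wilcoxon tests, an ANOVA for AUC and Cmax, and geometric mean ratios with 90% confidence intervals.

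**Aim.** The Pharmacogenomics background says "The current study aim is to evaluate the best rifabutin dosing regimen when coadministered with lopinavir/ritonavir in HIV-infected patients".

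**The concern.** A reader cannot tell from the protocol whether the comparison with RBT alone is the main result or a secondary one. Section 2 and the summaries say secondary; section 3.1 says primary. An analysis plan can refine a primary objective, but it should not have to choose between two conflicting statements in the protocol it serves.

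The analysis section does not settle the matter, because its comparisons are not those of section 3.1. Section 3.1 compares doses and section 5.9 compares visits, and in a two-sequence cross-over these differ. Followed literally, section 5.9 would not estimate either primary contrast. Room is left for choosing, after the data are seen, which ranking and which comparison to present as the main finding.

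The contrast that bears most directly on choosing between the two regimens, daily v thrice-weekly RBT, is also the only one protected by randomisation, since RBT alone always comes first, at PK1. No objective in section 2 and no outcome in section 3 names it.

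**Working it through.** **1. Is it the same comparison under two ranks?** Section 2.2 speaks of bioavailability and section 3.1 of pharmacokinetics, so they might be thought to differ. The End-points paragraph of the summary measures the bioavailability of RBT by AUC0-24 against AUC0-24 for each dose with antiretrovirals. Section 3.1 measures its pharmacokinetic comparison in the same way. The doses, comparator and measure agree, so it is one comparison with two ranks.

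**2. The plan's own figure.** The 12 participants in section 4 cannot be reproduced, because neither a standard deviation nor a type I error rate is stated. If a paired test at two-sided 5% is assumed, 80% power with n = 12 needs a standardised difference of 0.889, so the implied SD of the paired difference is 20 / 0.889 = 22.5% of the mean. The figure matters here only because it shows which comparison the trial was sized for: the one in section 3.1.

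**3. What the visit comparisons estimate.** Sections 2.1 and 5.4 (treatment arms, follow-up) give these regimens:

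| Arm | PK1 | PK2 | PK3 |
|---|---|---|---|
| A | RBT alone | thrice weekly + LPV/r | daily + LPV/r |
| B | RBT alone | daily + LPV/r | thrice weekly + LPV/r |

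Write the mean log AUC as m0 (RBT alone), mT (thrice weekly) and mD (daily). Let p be any shift from PK2 to PK3 unrelated to dose, and f the share of patients in arm A. Then:

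- Mean at PK2 = f·mT + (1 − f)·mD
- Mean at PK3 = f·mD + (1 − f)·mT + p
- PK3 − PK2 = (2f − 1)(mD − mT) + p

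With 16 per arm, f = 1/2, so:

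- PK2 − PK1 = (mT + mD)/2 − m0, the average of the two doses against RBT alone
- PK3 − PK2 = p, with no dose effect left in the mean

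**4. Illustration with section 4's 20%.** Suppose, for illustration only, that the exposure ratios to RBT alone are 1.20 for one dose and 0.80 for the other.

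- The true dose contrasts are 1.20 and 0.80, and the ratio between doses is 1.20 / 0.80 = 1.50.
- PK2 v PK1 gives √(1.20 × 0.80) = √0.96 = 0.98.
- PK3 v PK2 gives 1.00 apart from p.
- If attrition leaves 16 patients in one arm and 12 in the other, |2f − 1| = 4/28 = 1/7, and the 1.50 would appear as 1.50^(1/7) = 1.06, or its inverse.

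Two doses that each differ from the reference by the amount the trial is sized to detect would look equal to it and to each other.

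**5. Is daily v thrice-weekly named elsewhere?** Secondary objective 1 compares both doses with RBT alone. Secondary objective 3 concerns tuberculosis outcomes under either dose. Outcome 1 in section 3.2 concerns lopinavir, not RBT. The last sentence of section 4 compares patients starting on the high dose with those starting on the low dose, which is a sequence comparison. None of these is the within-patient RBT contrast.

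**The case against.** **The operative text largely agrees.** Section 3.1, section 4 and the End-points paragraph of the summary all point to AUC0-24 of each dose against RBT alone. Only the ranking in the objectives lists differs. That is true, and it makes this a conflict of labels rather than a trial without a primary comparison. It also shows which way to resolve it.

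**Section 5.9 may be shorthand.** An analyst would probably compare by dose, and the ANOVA could carry dose, period and sequence terms. Alternatively, the visits may be meant within each arm, where PK1 v PK2 in arm A is thrice weekly v RBT alone. Either is plausible, but section 5.9 states neither. Read within arm, each dose contrast splits into two estimates, and PK2 v PK3 confounds dose with period. Model terms can be left to an analysis plan; the contrasts themselves should match section 3.1.

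**The aim may not need daily v thrice-weekly.** The quoted aim comes from the pharmacogenomics background, and each dose could be judged by its exposure relative to RBT alone. This is fair. It supports a key secondary place for that contrast, not a primary one.

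**A stronger reading on error rates.** A reader might infer that several unranked contrasts and measures inflate the type I error by a definite multiple, such as 1.8, and that the protocol must split alpha. The documents do not support this:

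- No alpha is stated. At an assumed two-sided 5%, two contrasts sharing PK1 give 0.0907, or 1.81 times, at correlation 0.5, but 0.0704, or 1.41 times, at correlation 0.9. So 1.8 is not a floor.
- Those rates assume that all three exposures are equal. The two regimens supply 7 × 150 = 1,050 mg and 3 × 150 = 450 mg of RBT per week with the same LPV/r dose, a ratio of 7:3. If their exposures differ, they cannot both equal the reference. At most one pairwise null is then true on a given AUC, and the chance of a false rejection on that measure is at most the per-test level.
- Sections 3.1 and 3.2 already make RBT AUC primary and lopinavir AUC secondary. Cmax, trough, Tmax and half-life are primary nowhere, so counting them in one family is not justified.
- For a phase II PK study reporting ratios with 90% intervals, formal multiplicity control is debatable and may lie in an analysis plan that is not shown.

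**Conclusion.** The point holds as an internal contradiction with a consequence for the analysis. One comparison is ranked secondary in section 2.2 and in both summaries, and primary in section 3.1, where it is also the basis of the sample size. The comparisons in section 5.9, read as written and pooled over arms, are period contrasts. With equal arms they return the average of the two doses against RBT alone and carry no information in the mean difference about daily v thrice-weekly.

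That result rests on the cross-over layout in sections 2.1 and 5.4 and on a literal, pooled reading of section 5.9. The 1.20 and 0.80 ratios are illustrative, not predicted. No inflation of the error rate is claimed, and the documents do not leave the primary PK measure open to choice between AUC and Cmax. The matter should be corrected, but it does not threaten the design.

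**What to change.** - **Section 2 and both summaries:** move secondary objective 1 to primary, so that they agree with sections 3.1 and 4. The present descriptive statement can stay as the overall aim.
- **Sections 3.1 and 5.9:** define the primary contrasts by dose, as the geometric mean ratio of AUC for each RBT dose with LPV/r to RBT alone. As section 3.1 gives both AUC0-24 and AUC0-48 for the thrice-weekly dose, say which one the ratio uses.
- **Sections 3.2 and 5.9:** name the within-patient daily v thrice-weekly RBT AUC ratio as the key secondary contrast, and replace PK2 v PK3 by dose-defined wording for lopinavir as well.
- **Section 5.9:** describe Cmax, trough, Tmax and half-life as supportive.

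The cost is wording in sections 2, 3 and 5.9 and in the two summaries. It needs no new patients, visits, samples or data, and no alpha split.
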